##### Child mental health

The child depression and anxiety subscales of the BASC-2 questionnaire will be used to assess child mental health. At the 5 year clinic appointment, a small sample of the child’s hair will be collected for measurement of hair cortisol as an indicator of chronic stress. Hair samples (around 100 hairs in total) will be obtained from the vertex posterior region (the back of the head in a line between tops of ears) of the scalp, and stored for later analysis of cortisol [98, 99].

##### Parenting practices

Discipline will be assessed using one question: “please state which of the following you have done to get your child to do, or to stop doing, something over the past week?” followed by a list of 14 common discipline strategies on which respondents will indicate the number of days (0 to 7) that strategy had been used in the last week.

##### Maternal mental health

Maternal mental health will be determined using the Depression, Anxiety and Stress Scale (DASS 21), a widely used 21 item quantitative measure covering depression, anxiety (symptoms of psychological arousal), and stress (the more cognitive, subjective symptoms of anxiety) [100].

Four additional measures will be collected but are not discussed here as they will not be part of the main analyses: child salivary oxytocin (5 years of age), maternal salivary oxytocin (child 3.5 years of age), child blood pressure (3.5 and 5 years of age), and awake heart rate variability in children lying supine followed by heart rate responses to a 70° head-up tilt test (3.5 and 5 years of age).

### Analysis

For the key objectives, data will be analysed using linear, logistic (binary or ordinal), and Poisson (or negative binomial) regression models to compare the four arms of the trial in terms of continuous, categorical (binary or ordinal), and count outcomes respectively, with a random effect for participant along with terms for age and a group-by-age interaction added when longitudinal outcomes are analysed. As analyses at 2 years did not find consistent evidence in support of interactions between the Sleep and FAB interventions, we also plan to investigate outcomes using combined Sleep and combined FAB groups. A two stage process will be used, first investigating whether there is evidence for such an interaction (a reparameterisation of the four group model) and if not, the Sleep and FAB intervention terms will be investigated without the interaction included, although this process will increase the Type I error rates beyond the nominal level [101]. All *P*-values will be reported using three decimal places and *p*-values less than 0.001 will be reported as ‘*p* < 0.001’. Two-sided *p* < 0.05 will be considered to indicate statistical significance and no adjustments for the multiple outcomes are planned. Post-hoc comparisons between the three intervention and one control groups will only be performed where the overall (Wald) test is statistically significant. Where available, baseline values will be included in models and all models will include the stratification variables [102]. Standard model diagnostics will be used and log-transformations used where this improves residual normality and/or homoscedasticity for continuous outcomes. Homser-Lemeshow tests will be used for binary logistic regression models and proportionality will be assessed in ordinal logistic regression models using generalised ordinal logistic regression. Overdispersion will be examined using a likelihood ratio test for count outcomes, with negative binomial regression used when this is significant. Where model residuals remain unacceptable for continuous outcomes, quantile regression, including mixed quantile regression where appropriate, will be used instead to model medians.

Similar models will be used for the additional objectives with the study group included but not of direct interest in itself. No subgroup analyses are currently planned. All effect sizes will be accompanied by 95 % confidence intervals and these will be used to assess clinical significance alongside determination of statistical significance. As missing data is expected to be around a quarter of the original participants and is unlikely to be MCAR or even MAR when conditioning only on the intervention group and stratification variables alone, all analyses will be accompanied by sensitivity analyses using multiple imputation with predictors including previously available outcome measures where possible and using chained equations when necessary. Rubin’s method for combining the results from the 25 imputations (or more if necessary such that the number of imputations exceeds the percentage of missing data) will be used. Scenario analyses will be performed to explore the robustness of findings to models of informative missingness [103]. Current or subsequent versions of Stata (14.1 or later) and R (3.3.1 or later) will be used for all analyses. Statistical analyses will be conducted by one of the co-investigators (AG) who also performed analyses on outcomes at earlier times.

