In 2009, we commenced the POI (Prevention of Overweight in Infancy) RCT in 802 Dunedin families designed to reduce the number of children with excessive weight gain in the first 2 years of life [38]. Participants were randomised to one of four groups: Control (usual care), FAB (food, physical activity and breastfeeding), Sleep, or Combination (received FAB and Sleep interventions). All four groups received standard Maternity and Well Child care [39], and the three intervention groups received additional guidance and support on the relevant behaviours (breastfeeding, diet, physical activity, sleep) as detailed previously [38, 40, 41]. The POI study, and the three large controlled trials from Australia (Healthy Beginnings [42], Nourish [43], and InFANT [44]), are combining their data to form a prospective meta-analysis of the feasibility and effectiveness of early obesity prevention efforts (Early Prevention of Obesity in Children, EPOCH) [45]. Care has been taken to ensure that the study design, participants, intervention, comparators and outcome measures are similar across all four studies.

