Other factors of interest in child growth include physical activity, diet and the gut microbiota. How physical activity patterns develop is of interest given the low rates of physical activity seen in some [65, 66], although not all [67], studies in young children, and the observation that marked declines in activity are apparent even in the preschool years [68]. Accelerometers are increasingly being used to measure physical activity in children under five years of age [69], although rarely in those less than 3 years of age [70, 71]. 24-h accelerometry data (over 5 days) were collected at 6, 12 and 24 months as part of POI to measure both sleep and physical activity [72], and extending these measures in our follow-up study will allow us to examine multiple questions of interest regarding the early development of physical activity and inactivity and sleep. How the gut microbiota develop in early life and the potential relationship with obesity is of intense interest worldwide [73]. Despite clear differences in bacterial composition between lean and obese mice, corresponding findings in studies of humans have been considerably more mixed [74–76]. However, several longitudinal studies have now demonstrated that variation in gut microbiota during infancy is related to overweight status at older ages [77–79], although existing studies contain few subjects [77, 78] or use parent-reported BMI values [79] which have known inaccuracies [80]. Many studies are also unable to account for dietary intake, which clearly alters the bacterial composition of the microbiome [76]. Although it remains to be seen whether variation in gut microbiota is a cause or consequence of obesity [81], our prospective study includes a large number of children whose diet and lifestyle since birth has been well documented.

The overall aim of the POI follow-up is to determine the extent to which augmented parental support and education on infant sleep, feeding, diet, and physical activity in the first 2 years of life reduces BMI at 3.5 and 5 years of age, and to determine the role of self-regulation in any such relationship.

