## Methods/Design

### Study design and participants

The POI study was a four-arm RCT controlled trial assessing whether additional education and support on sleep (Sleep group); breastfeeding, diet, and physical activity (FAB group); or both (Combination group) reduced excessive weight gain from birth to 2 years of age compared to usual care (Control group) [38]. All mothers who had booked into the single maternity hospital (>97 % of all births) serving the city of Dunedin, NZ, between May 2009 and November 2010 were invited to participate in the POI study when they were 28–30 weeks gestation. Exclusion criteria applied before birth were: home address outside Dunedin, planning to move from Dunedin in the next 2 years, booked into the maternity centre after 34 weeks gestation, or unable to communicate in English or Te Reo Māori (language of the indigenous (Māori) ethnic group of NZ). Exclusion criteria applied after birth were: identification of a congenital abnormality likely to affect feeding or growth, or birth before 36.5 weeks gestation. All participants enrolled in the original POI intervention will be invited to participate in follow-up measurements by research staff. The study was approved by the University of Otago Human Ethics Committee (12/274) and written informed consent will be obtained from participants before commencing the first follow-up visit at 3.5 years of age.

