### Data collection

All data will be collected via two clinic visits lasting 60–90 min, one when the child is 3.5 years, and the other when they are 5 years of age. In brief, the child and parent(s) will have their height, weight and waist circumference measured, and the parent completes the questionnaire while the child undergoes the neuropsychological measures of self-regulation and a hair sample is taken (see below). One week later, parents will be contacted and the accelerometer, remaining questionnaire items, 24-h microbiota food frequency questionnaire, and stool sample will be collected. The dual-energy x-ray absorptiometry (DXA) scan will occur at a separate visit within two weeks of the clinic visit (5 years of age only). Parents will be compensated with a $20 grocery voucher for attending the clinic visit and a $10 grocery for completing the take-home questionnaire. Children will be offered a story book of their choice as a gift. Families who have since left the area but want to continue participating will be able to arrange to have their child (and themselves) weighed and measured at a medical centre, and complete online questionnaires. No other measurements will be obtained for these out-of-town participants.

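### The 3.5- and 5-year visits fall in roughly opposite seasons and the listed models carry no season term: an avoidable loss of precision for activity, sleep and dietary patterns, and a partial mixing of season with age in the cohort analyses

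*Protocol article*

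**What the plan says.** Under Data collection, everything is collected around two clinic visits, "one when the child is 3.5 years, and the other when they are 5 years of age". No visit window is stated. Accelerometer activity and sleep come from one five-day recording per visit, and the food frequency questionnaire refers to the past month. Table 1 lists accelerometer outcomes and dietary pattern scores at both ages, and nutrient intake at 5 years only.

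Under Analysis, the key-objective models serve "to compare the four arms of the trial in terms of continuous, categorical (binary or ordinal), and count outcomes respectively". Where an outcome is measured at more than one age, the same section extends the model "with a random effect for participant along with terms for age and a group-by-age interaction added when longitudinal outcomes are analysed". On other covariates: "Where available, baseline values will be included in models and all models will include the stratification variables". The article does not name the stratification variables. Similar models are to be used for the additional objectives. No season, month or measurement date appears among the terms.

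Under Study design and participants, mothers booked into the maternity hospital "between May 2009 and November 2010 were invited to participate in the POI study when they were 28–30 weeks gestation".

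Two places look beyond the arm comparison. The Background says that extending the accelerometry begun at 6, 12 and 24 months will make it possible to "examine multiple questions of interest regarding the early development of physical activity and inactivity and sleep". The additional objectives and the Discussion part of the Abstract plan cohort analyses of the predictors and development of BMI, self-regulation and sleep consolidation.

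**The concern.** Eighteen months is one and a half seasonal cycles. A child first measured in summer is next measured in winter, and the reverse. Five days of accelerometry or one month of recalled diet captures a single season. If an outcome varies with season, its seasonal component changes sign between a child's two visits. A random effect for participant, read as a random intercept, is constant within the child and cannot absorb a component that flips.

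Two things are at stake. In arm contrasts for seasonal outcomes, the seasonal component stays in the error although the date of measurement could remove it. In cohort work on how sleep or activity develops, part of each child's apparent change with age may be season. The same holds for models relating an earlier activity or sleep measure to a later one when the two were taken half a cycle apart.

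**Working it through.** **Inputs from the protocol article.** Visit ages 3.5 and 5 years. Recruitment May 2009 to November 2010, counted as 19 months. Four randomised arms, at least 600 children at 5 years, so 150 per arm if equal. The article gives no figure for a seasonal effect, so there is none to reproduce.

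**Assumptions.** The seasonal effect is A·cos(2π(t − p)/12), with t in months, peak at p and half-amplitude A. Births are uniform over the recruitment span. Outside season, the outcome has SD 1 and within-child correlation 0.5. A runs from 0 to 0.5 SD.

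**1. One child.** (5 − 3.5) × 12 = 18 months, which is half a cycle out of phase. With phase θ at 5 years, the seasonal part is A·cos θ at 5 years and −A·cos θ at 3.5. The change contains 2A·cos θ, so it is shifted by up to 2A either way. If the gap is off by m months, the maximum becomes 2A·cos(πm/12): 97% of 2A for one month and 87% for two. The point therefore needs visits near schedule, not an exact gap.

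**2. Earlier accelerometry.** Relative to birth month, ages 6, 12, 24, 42 and 60 months fall in the opposite, same, same, opposite and same season. Three of the four steps (6 to 12, 24 to 42, 42 to 60) reverse season.

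**3. Cohort mean change.** Averaging 2A·cos θ over a birth window of L months with midpoint M gives

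2A × [sin(πL/12)/(πL/12)] × cos(2π(M − p)/12).

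For L = 19 the bracket is −0.966/4.974 = −0.194. The largest possible shift is 2 × 0.194 = 0.39A, or 19% of peak-to-trough (2A). The smallest is 0, when M and p are a quarter-cycle apart. Cases:

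- Window marks invitations, so births start about mid-July 2009; mid-January peak: 0.10A (5% of peak-to-trough).
- Window marks births, starting May 2009; mid-January peak: 0.34A in absolute size (17%).
- Births from mid-July 2009; mid-April peak: 0.38A in absolute size (19%).
- An 18-month window would raise the ceiling to 0.42A; a 12- or 24-month window gives 0.

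**4. Arm contrasts.** Randomisation balances birth month in expectation, so the seasonal part has the same expected mean in every arm. In a simulation of 4 × 150 children without a season term, bias in the group-by-age contrast was 0.003 SD or less (simulation noise), and type I error was 0.048 to 0.051 for A = 0.2 to 0.5.

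Precision follows in closed form. The non-seasonal variance of a change is 2(1 − 0.5) = 1, and season adds 4A² × ½ = 2A². At one age the variance goes from 1 to 1 + A²/2.

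| A (SD) | SE of change contrast, √[(2/150)(1 + 2A²)] | Increase | Increase at a single age, √(1 + A²/2) |
|---|---|---|---|
| 0 | 0.115 | – | – |
| 0.2 | 0.120 | 4% | 1% |
| 0.3 | 0.125 | 9% | 2% |
| 0.5 | 0.141 | 22% | 6% |

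The simulated standard errors (0.112, 0.118, 0.125, 0.142) agree closely.

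**5. Effect of adding the term.** In a further simulation (2,000 runs; births from mid-July 2009, mid-January peak, A = 0.5), adding sine and cosine of date lowered the SE of the change contrast from 0.141 to 0.115, and the spurious mean age change from 0.049 to 0.000. Births cover all calendar months, so age and season can be estimated separately.

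**The case against.** The strongest reply is that the listed models compare randomised arms, every key objective is an arm difference, and randomisation removes bias from those contrasts. That stands. At a single age the loss of precision is small over the assumed range.

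It can also be said that a condensed article need not list every secondary covariate, and that a full analysis plan may include month of measurement. That is fair, and nothing in the article is contradicted on this point. The article does, however, name its covariates and extends similar models to the cohort objectives, so it is reasonable to ask that the date of measurement be among them.

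Third, mean age change in activity or diet is not a stated objective. The remark on activity development is Background text. Sleep consolidation is the only outcome at issue that is named in the cohort objectives. This limits the reach of the point but does not remove it.

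A reader might infer more than the documents support:

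- That every child is measured exactly half a cycle apart. No visit window is given, so this holds only near schedule.
- That season and age are fully confounded. Births span all calendar months, so opposite shifts largely cancel and the remainder depends on the assumed window and peak.
- That the arm comparisons or the primary analysis are biased. They are not.
- That all diet outcomes are affected longitudinally. Nutrient intake is measured at 5 years only, so only dietary pattern scores have a change between these visits.

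**Conclusion.** The point holds as a low-cost improvement to secondary and cohort analyses; it does not identify an error in the primary analysis. For accelerometer activity, sleep and dietary pattern scores, leaving out season keeps removable variance in the contrasts: about 4% on the standard error of a change contrast at A = 0.2 SD and 9% at 0.3 SD, less at a single age. In cohort analyses of development, one child's change can be shifted by up to 2A, and the cohort mean change by about 0 to 0.39A.

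These sizes rest on a sinusoidal season effect, uniform births over 19 months, visits near schedule and a within-child correlation of 0.5. The documents give neither A nor the seasonal peak, and A may be negligible for some outcomes. If so, the added term changes little.

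**What to change.** In the Analysis section, for accelerometer activity, sleep timing and duration, and dietary pattern scores, add season at the date of measurement as a fixed covariate, using sine and cosine of day of year, or day length. Use the recording dates for accelerometry and the recall month for diet. Do the same in the similar models for the additional objectives wherever these measures are outcomes or predictors, using the date of each measurement. Report any change with age in these outcomes season-adjusted. The models for BMI z-score need no change on this account.

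The cost is two degrees of freedom per model with sine and cosine (one with day length) and a little more analysis work. No new data are needed: the measurement date is already required to calculate age for the z-scores.

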## Background

Globally, it is estimated that 42 million children are overweight or obese, illustrating the seriousness of this public health challenge [1]. The prevalence of childhood obesity has increased substantially since the 1970s and there is little evidence to suggest these rates are tapering off [2, 3]. It is clear that New Zealand (NZ) children are following this global trend, with 9.5 % of children being obese by the time they are only 2–4 years of age and a further 20 % being overweight [4]. In addition to the immediate adverse effects of obesity in infancy and toddlerhood [5], it is also a strong risk factor for overweight later in life, and the associated health effects [6]. Determining the most effective tools for reducing excessive weight gain early in life is paramount if we are to prevent obesity before it becomes entrenched [7].

The early years are a time of immense change when fundamental behaviours including those around eating, sleeping, and physical activity are established. It is apparent that overweight and obesity develop from the complex interaction of multiple factors [8, 9], including biological effects (e.g. genetic susceptibility [10], and an ‘obesogenic’ gut microbiome [11]), behavioural factors (e.g. dietary, physical activity, sedentary and sleep habits [12, 13]), as well as cultural, social, environmental and economic influences [14, 15]. Evidence also suggests that parenting and discipline practices [16–18], mental health [19], and infant temperament [20, 21] may influence the development of obesity in young children. It has recently become apparent that many of these factors are influenced by self-regulation – the ability to control one’s behaviour without external assistance [22, 23]. To gain traction in reducing childhood obesity rates, interventions need to modify a wide range of these factors.

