All four EPOCH studies aimed to modify BMI in the first 2 years of life through food, parenting and physical activity interventions. However, in addition to targeting these behaviours, the POI study also included a sleep intervention arm. Whether sleep interventions can affect growth trajectories is not known, but is an area of great interest internationally [46]. We know that adequate sleep in infancy and childhood is important for behaviour, learning and family functioning [47] but a wealth of data now link poor sleep habits with an increased risk of overweight in childhood as well [13, 48–50]. Despite this, we know relatively little about whether it is possible to change sleep behaviour and ultimately affect growth because very few sleep interventions have been published to date [26, 51–53]. Our brief POI intervention (2 core visits) focused on developing appropriate sleep habits from birth, including the ability of the infant to regulate their own sleep, i.e. to fall asleep when tired without external aids such as being fed to sleep or being rocked in a parent’s arms [54]. At 2 years of age, we observed no significant intervention effect on mean BMI across the four study groups. However, an exploratory analysis demonstrated that when the two groups receiving the sleep intervention (Sleep and Combination) were combined, the sleep intervention halved the odds of obesity (BMI ≥95th percentile) compared to the groups who did not receive the sleep intervention (Control and FAB) [55]. It thus seems opportune to follow-up this cohort to determine, first, whether this effect on obesity is sustained, and second, the mechanism by which a sleep intervention might beneficially affect weight in young children.

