### Sample size

Retention at 2 years was 86 % (*n* = 686/802) which is higher than was anticipated in our original power calculations (20 % loss to follow-up was assumed) [38]. Based on this, we anticipate retaining at least 75 % of the original cohort through to age five, giving us an estimated sample size at 5 years of at least 600 participants. This would provide 80 % power to detect a difference in BMI of 0.3 kg/m^2^ or larger at 5 years of age between any pair of the four groups using a two-sided test at the 0.05 level, based on earlier data from this research group suggesting a standard deviation of 0.8 [49]. This sample size would also allow 80 % power for detecting differences in self-regulation scores of 0.35 standard deviations between any two arms of the trial (falling between a “small” and “moderate” effect size) and detecting correlations at the study level of 0.12 or larger between continuous measures (e.g. between parenting style at 12 months and self-regulation at 5 years and between consolidated sleep hours at 6 months, and self-regulation at 3.5 and 5 years) using two-sided tests at the 0.05 level.

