### Outcome measures

The timing of the outcome measures is presented in Tables 1 and 2. All measures are undertaken by trained research staff blinded to original group allocation.

**Table 1 Tab1:** Outcome measures used to determine the effects of the POI intervention in children at 3.5 years and 5 years of age

				Age	
	Measure	Method	Objectives	3.5 years	5 years
Anthropometry	Height, weight	WHO Growth standards [83]	a	Child	Child
	BMI	Calculated	a	Child	Child
	BMI-for-age z-score	WHO Growth standards [83]	c	Child	Child
	Prevalence of overweight	BMI z-score ≥85th but <95th percentile	c	Child	Child
	Prevalence of obesity	BMI z-score ≥ 95th percentile	c	Child	Child
	Waist circumference	WHO Growth standards [83]	c	Child	Child
Self-regulation	Overall self-regulation	NEuroPSYchological Assessment (NEPSY) [63]	b	Child	Child
		Head-Toes-Shoulders-Knees task [64]	b	Child	Child
		Behavior Assessment System for Children (BASC) [85]	b	Child	Child
		Child Behavior Questionnaire [86]	b	Child	Child
	Sleep-related self-regulation	Researcher generated	b	Child	Child
	Energy self-regulation	Children’s Self-Regulation in Eating scale [87]	b	Child	Child
Body composition	Body fat %	Dual-energy X-ray absorptiometry (DXA) scan	d	-	Child
	Lean mass %	Dual-energy X-ray absorptiometry (DXA) scan	d	-	Child
Sleep	Sleep timing	Accelerometry [104]	e	Child	Child
	Sleep duration	Accelerometry [104]	e	Child	Child
	Awakenings	Accelerometry [104]	e	Child	Child
	Sleep problems	Researcher generated	e	Child	Child
	Sleep hygiene	Researcher generated	e	Child	Child
	Sleep disturbances	Sleep Disturbance Scale for Children [94]	e	-	Child
Physical activity	Physical activity	Accelerometry [72]	f	Child	Child
	Sedentary behaviour	Researcher generated	f	Child	Child
Diet	Dietary pattern scores	Food frequency questionnaire [96]	g	Child	Child
	Nutrient intake	Food frequency questionnaire [95]	g	-	Child

**Table 2 Tab2:** Additional measures collected to determine the predictors of BMI, self-regulation, and sleep consolidation at 3.5 years and 5 years of age

			Child		Parent	
	Measure	Method	3.5 years	5 years	Child age 3.5 years	Child age 5 years
Child gut microbiota	Gut microbiota	From stool sample	Child	Child	-	-
Child mental health	Child depression	BASC-2 [85]	Child	Child	-	-
	Child anxiety	BASC-2 [85]	Child	Child	-	-
	Child stress	Hair cortisol [99]	-	Child	-	-
Parenting practices	Discipline	Researcher generated	-	-	Mother	Mother

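### If obesity at 3.5 and 5 years is fitted jointly with a random effect per child, the planned odds ratio is conditional on the child, while the objective concerns prevalence in the groups

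*Protocol article*

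**What the plan says.** The Analysis section of the protocol article sets the model family: "data will be analysed using linear, logistic (binary or ordinal), and Poisson (or negative binomial) regression models to compare the four arms of the trial". For repeated outcomes it continues: "with a random effect for participant along with terms for age and a group-by-age interaction added when longitudinal outcomes are analysed".

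Table 1 (Outcome measures) defines obesity as "BMI z-score ≥ 95th percentile" and schedules it, like overweight, at both 3.5 and 5 years. The third key objective at the end of the Background (objective c in Table 1) asks whether the interventions lead to differences in the prevalence of overweight or obesity at those ages.

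The Background explains why this outcome matters. In an exploratory analysis at 2 years, "the sleep intervention halved the odds of obesity (BMI ≥95th percentile) compared to the groups who did not receive the sleep intervention". The first stated reason for the follow-up is to learn "whether this effect on obesity is sustained". The Analysis section also says how estimates will be read: "All effect sizes will be accompanied by 95 % confidence intervals and these will be used to assess clinical significance".

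The article does not mention marginal standardisation, generalised estimating equations or any other conversion of the mixed-model odds ratio to the group level.

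**The concern.** A logistic model with a random intercept per child compares the odds of obesity for two children who share the same latent risk and differ only in group. Prevalence is an average over children whose latent risks differ. The odds ratio is non-collapsible, so the two quantities differ whenever there is an effect and the random-effect variance is above zero, and the conditional one is always further from 1. The gap grows with that variance, which is driven by how strongly obesity tracks within a child between the two visits.

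The size of the reported odds ratio would therefore reflect both the intervention and the tracking. A reader who takes it as the ratio of the odds of obesity between groups would overstate the effect. A reader who sets it against a group-level halving at 2 years could take a change of scale for persistence or strengthening. The same holds for any other binary or ordinal outcome analysed jointly over the two ages.

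**Working it through.** **Plan's own figure.** There is none to reproduce. The sample-size section covers BMI, self-regulation scores and correlations, and gives no figure for obesity.

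**Inputs.**
- Prevalence without the sleep intervention: p0 = 9.5%, from the national figure in the Background, "9.5 % of children being obese by the time they are only 2–4 years of age".
- Group-level (marginal) odds ratio: 0.50 at both ages, taken for illustration from the 2-year result.
- Latent within-child correlation ρ: not in the article, so assumed, from 0.3 to 0.9.

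**Step 1: group-level target.** Odds without the intervention = 0.095/0.905 = 0.1050. Half of that is 0.0525, so p1 = 0.0525/1.0525 = 5.0%. The difference is −4.5 percentage points and the prevalence ratio is 0.53.

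**Step 2: random-effect SD.** On the logistic scale ρ = σ²/(σ² + π²/3), so σ = √[ρ/(1−ρ) × π²/3]. For ρ = 0.6: σ = √(1.5 × 3.290) = 2.22.

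**Step 3: conditional odds ratio.** In each group find the intercept a for which the average of 1/(1+exp(−(a+σz))) over a standard normal z equals that group's prevalence. The conditional odds ratio is exp(a1 − a0). For ρ = 0.6: a0 = −3.723, a1 = −4.705, and exp(−0.982) = 0.37.

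| ρ | σ | Conditional OR when marginal OR = 0.50 | Ratio of log odds ratios |
|---|---|---|---|
| 0.3 | 1.19 | 0.46 | 1.12 |
| 0.5 | 1.81 | 0.41 | 1.28 |
| 0.6 | 2.22 | 0.37 | 1.42 |
| 0.75 | 3.14 | 0.29 | 1.77 |
| 0.9 | 5.44 | 0.15 | 2.78 |

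The prevalences are 9.5% and 5.0% in every row.

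**Step 4: check with a different data-generating model.** Obesity status was obtained by cutting a bivariate normal BMI z-score with correlation r between the visits. The planned model (group, age, group-by-age, random intercept) was then fitted by maximum likelihood to the exact cell probabilities. At 9.5% the odds ratio at each age is 0.41, 0.37, 0.33, 0.26 and 0.15 for r = 0.5, 0.6, 0.7, 0.8 and 0.9. At r = 0.7 and 0.8, 46% and 56% of children obese at 3.5 years are still obese at 5.

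**Step 5: the reverse direction.** Suppose the mixed model reports 0.50. At 9.5% prevalence the marginal odds ratio is then 0.54, 0.58, 0.62, 0.68 or 0.78 at ρ = 0.3, 0.5, 0.6, 0.75 or 0.9. At ρ = 0.75 this means 9.5% against 6.7%, compared with 9.5% against 5.0% for a true group-level halving.

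**Sensitivity to prevalence.** Over ρ = 0.5 to 0.9 the conditional odds ratio runs from 0.43 to 0.17 at 5% prevalence and from 0.39 to 0.13 at 15%. For overweight and obesity together (9.5% + 20% = 29.5%) it runs from 0.36 to 0.10.

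**The case against.** The strongest reply is that the article does not commit to the problem. The random effect enters only when longitudinal outcomes are analysed, and no sentence says that obesity will be fitted jointly over both ages. The objective can be read as a comparison at each age. The planned Hosmer–Lemeshow tests belong to ordinary logistic regression, which suggests that single-age models are at least in view. This stands as a limit: the point applies if the joint fit is used. But the rule is written for outcomes of exactly this kind, and the text does not exempt obesity.

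A second reply is that the random-intercept model is a standard and valid analysis, and that the choice of reported effect measure can be left to the analysis plan. The first half is right, and the model should stay. The second half carries less weight here, because the article itself fixes the model, states a prevalence objective and says that effect sizes will be read for clinical significance.

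Third, covariate adjustment also makes an odds ratio conditional. All models include the stratification variables, so a single-age logistic model is not strictly marginal either. That is true, and standardising over the covariates removes this as well.

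A reader might infer more than the article supports, in four ways:
- **That the odds ratio will be far too extreme.** This depends on a correlation that is not given. At ρ = 0.3 the shift is only from 0.50 to 0.46.
- **That its size reflects tracking and not the intervention.** It reflects both. With no intervention effect the conditional odds ratio is 1.
- **That the significance test is invalid.** The null value is 1 on both scales, and the confidence interval is on the same scale as the estimate.
- **That the 2-year odds ratio is known to be group-level.** The article does not show the model behind it, and does not commit to a numerical comparison.

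**Conclusion.** The mismatch between model and objective is real, within limits. Under a joint fit, the planned odds ratio for obesity answers a different question from the prevalence objective and lies further from 1. For a marginal odds ratio of 0.50 at about 10% prevalence the conditional value is about 0.46 under weak tracking (ρ = 0.3) and about 0.15 under very strong tracking (ρ = 0.9). The direction is certain for any real effect with a non-zero random-effect variance. The size rests on the assumed correlation, prevalence and true effect.

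What is affected is the estimate, its interval, the judgement of clinical significance and any comparison with 2 years. If the 2-year odds ratio was itself conditional, the comparison would be sound only if the random-effect variances were similar. The primary BMI z-score is analysed with a linear model, where conditional and marginal mean differences coincide, so it is untouched. Obesity prevalence is a secondary outcome, though it is the one that motivated the follow-up.

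**What to change.** Keep the mixed model. Add a sentence to the analysis plan: for binary outcomes measured at both ages (and for ordinal outcomes, by category), the main effect measure is the standardised marginal prevalence by group at each age, integrated over the random effect and averaged over the covariates. Report it with the difference in prevalence and the marginal odds ratio, each with a 95% CI. Judge whether the effect is sustained from these figures, with the 2-year estimate expressed on the same scale. A separate logistic model at each age is an acceptable alternative.

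The cost is a post-estimation step in Stata or R, which the article already names. No new data are needed. The downside is that the reported odds ratios will look less extreme.
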